## Abstract

**Background:**

Progressive difficulty in performing everyday functional activities is a key diagnostic feature of dementia syndromes. However, not much is known about the neural signature of functional decline, particularly during the very early stages of dementia. Early intervention before overt impairment is observed offers the best hope of reducing the burdens of Alzheimer disease (AD) and other dementias. However, to justify early intervention, those at risk need to be detected earlier and more accurately. The decline in complex daily function (CdF) such as managing medications has been reported to precede impairment in basic activities of daily living (eg, eating and dressing).

**Objective:**

Our goal is to establish the neural signature of decline in CdF during the preclinical dementia period.

**Methods:**

Gait is central to many CdF and community-based activities. Hence, to elucidate the neural signature of CdF, we validated a novel electroencephalographic approach to measuring gait-related brain activation while participants perform complex gait-based functional tasks. We hypothesize that dementia-related pathology during the preclinical period activates a unique gait-related electroencephalographic (grEEG) pattern that predicts a subsequent decline in CdF.

**Results:**

We provide preliminary findings showing that older adults reporting CdF limitations can be characterized by a unique gait-related neural signature: weaker sensorimotor and stronger motor control activation. This subsample also had smaller brain volume and white matter hyperintensities in regions affected early by dementia and engaged in less physical exercise. We propose a prospective observational cohort study in cognitively unimpaired older adults with and without subclinical AD (plasma amyloid-β) and vascular (white matter hyperintensities) pathologies. We aim to (1) establish the unique grEEG activation as the neural signature and predictor of decline in CdF during the preclinical dementia period; (2) determine associations between dementia-related pathologies and incidence of the neural signature of CdF; and (3) establish associations between a dementia risk factor, physical inactivity, and the neural signature of CdF.

**Conclusions:**

By establishing the clinical relevance and biological basis of the neural signature of CdF decline, we aim to improve prediction during the preclinical stages of ADs and other dementias. Our approach has important research and translational implications because grEEG protocols are relatively inexpensive and portable, and predicting CdF decline may have real-world benefits.

**International Registered Report Identifier (IRRID):**

DERR1-10.2196/56726

## Introduction

### Background

Progressive difficulty in performing everyday functional activities is a key diagnostic feature of dementia. Yet not much is known about the neural underpinnings of functional decline, particularly during the very early stages of dementia. Early intervention before impairment in everyday functions is observed offers the best hope of reducing the burdens of Alzheimer disease (AD) and other dementias. However, to justify early intervention, those at risk need to be detected earlier and more accurately.

The decline in complex daily function (CdF) such as managing medications and finances has been reported to precede impairment in basic activities of daily living (eg, eating and dressing). Our goal is to establish the neural signature of decline in CdF during the preclinical dementia period. We recently reported that limitations in CdF were more prevalent or declined faster in those who converted to mild cognitive impairment (MCI) [1]. We compared CdF profiles at baseline in 59 community-dwelling older individuals with normal cognitive performance who went on to develop incident MCI (“pre-MCI”) with 284 older individuals who remained cognitively normal over follow-up. While limitations in CdF were reported to be subtle, the mean number of limitations at baseline was 3.1 (SD 3.0) in the pre-MCI cases and 2.0 (SD 2.4) in normal controls (*P*=.003). This is in line with studies using amyloid-β (Aβ), phosphorylated τ, neurofilament (also referred to as AT(N) classification system) [2] to stratify dementia risk in cognitively normal older adults, showing the presence of AT(N) biomarkers to be associated with more limitations in CdF [3,4].

While combining behavioral (eg, cognition and CdF assessment) with biological (eg, AT(N)) markers has further improved early risk assessment, it is insufficient to justify intervention during the preclinical dementia stages. For example, up to one-third of older individuals with significant accumulation of AD-related and vascular pathology will not progress to MCI and dementia stages [5,6]. In this proposal, we seek to further improve risk assessment by establishing the neural signature of CdF. We posit that abnormal patterns of neurophysiological activation precedes and can serve as a robust predictor of change in CdF, which in turn increases the risk of conversion to dementia [7]. To test this hypothesis, we designed complex gait tasks. Gait has physical and cognitive contributions. We showed that gait performance (eg, gait speed) during normal and dual-task conditions is associated with scores on the Activities of Daily Living–Prevention Instrument (ADL-PI) [8], which includes questions about abilities to manage money, drive, do the laundry, and use appliances [9,10]. We applied a novel electroencephalographic-based mobile brain-body imaging approach to measure gait-related brain activation while participants perform complex gait-based functional tasks [11-19]. Raising the complexity of the gait task may allow early distinction of individuals with and without the risk of developing limitations in CdF by increasing the cognitive demands of the task. We designed simple (walking-only) and complex (dual-task walking) gait-based tasks to measure differential activation (complex minus simple gait). This proposal builds on and extends 2 decades of work by our team showing that changes in gait (eg, slowing of walking speed) during simple and complex walking conditions are robust predictors of decline in CdF, cognitive decline, and progression to dementia [9,10,20-30].

### Hypothesis

Our overarching hypothesis illustrated in Figure 1 is that the presence of dementia-related pathology during the preclinical period of dementia is associated with a unique gait-related electroencephalographic (grEEG) pattern that predicts a subsequent decline in CdF. The first aim of this study is to establish the neural signature of CdF. Our preliminary findings show that individuals reporting CdF limitations can be characterized by weaker pre as well as postcentral gyrus and stronger fronto-medial activation during complex gait (eg, dual-task walking). This unique grEEG activation pattern (neural signature) will predict CdF decline longitudinally. Our second aim is to determine the association of dementia-related pathology with the incidence of the neural signature of CdF in individuals without the neural signature at baseline. Specifically, we hypothesize that plasma-based assays of Aβ, T, and white matter hyperintensities (WMH) at baseline will independently and in combination predict the incidence of the neural signature of CdF. We also need to understand if and how behaviors are known to increase dementia risk (eg, physical inactivity) and may modify the neural signature of CdF as a prelude to developing interventions. Our third aim is to determine whether physical inactivity is associated with the prevalence and incidence of the neural signature of CdF in our sample.

This project is part of a larger effort at the Division of Cognitive and Motor Aging at Albert Einstein College of Medicine (AECOM) to go beyond memory-centered depictions of AD and consider cognitive processes related to motor and sensory abilities as important additional characterization of AD and related dementias. We are partnered with an ongoing investigation (R01AG075679-01) that seeks to establish visual-somatosensory integration (VSI study) as a novel marker of preclinical AD. With Aβ accumulation occurring early in sensory association areas [31], the VSI study (principal investigator [PI] [name]) seeks to define multisensory integration as a preclinical marker of AD and related dementias (see [32] for more details). The VSI study serves as a parent study for cross-enrollment and includes older adults across the cognitive spectrum from cognitively normal to MCI. Participants in the VSI study with confirmed preclinical AD diagnosis (defined as Aβ positive) will undergo positron emission tomography testing. Collectively, these studies will broaden the scope of our investigations in synergistic ways to deepen our understanding of the very early preclinical dementia period.

**Figure 1 figure1:**
[figure not shown]
Sequence of events leading to decline in CdF. CdF: complex daily function; Cog.: cognitive; MCI: mild cognitive impairment; Unimp.: unimpaired.

## Methods

### Study Design and Recruitment

We propose a prospective observational cohort study of 180 older adults who are cognitively unimpaired. Figure 2 shows the recruitment and timeline of procedures. We will cross-enroll participants from an active study (R01AG075679, PI [name]). We will use telephone-based screening procedures to enroll and follow a community-based cohort. Potential participants aged 65 year and older from the greater New York City area are first contacted by mail and then by telephone to explain the purpose and nature of this study. The telephone interview includes verbal consent, a brief medical history questionnaire, and 2 brief cognitive screens [33,34]. We will ensure that enrollment reflects the race and ethnic diversity of our catchment area. Following the interview, potential participants are invited for further evaluation at our research center. If eligible, written informed consents are obtained at study visits as per institutional review board (IRB) guidelines. This study is approved by the AECOM IRB.

**Figure 2 figure2:**
[figure not shown]
Recruitment and procedures conducted under this proposal. Aβ: amyloid beta; CdF: complex daily function; CU: cognitively unimpaired; fun.: function; max.: maximum; MoCA: Montreal Cognitive Assessment; MRI: magnetic resonance imaging; T: phosphorylated τ; WMH: white matter hyperintensities.

### Study Criteria

#### Inclusion Criteria

Adults are included who are aged 65 years and older, can speak and write in English, reside in the New York metropolitan area, plan to be in the area for the next 3 or more years, and are ambulatory.

#### Exclusion Criteria

Exclusion criteria were previous MCI or dementia diagnosis, reported severe sensory impairments, chronic medication use (eg, neuroleptics) that influence cognitive functioning, terminal illness with life expectancy <12 months, existing diagnosis of neurodegenerative diseases (eg, Parkinson disease or amyotrophic lateral sclerosis), presence of clinical disorders that overtly alter attention like delirium, or major psychiatric disorder such as schizophrenia. Additional electroencephalographic and magnetic resonance imaging (MRI)–specific exclusion criteria are seizure medication, stroke, traumatic brain injury, claustrophobia, and MRI contraindications such as pacemakers or any permanent magnetic metal implants.

### Assessments

Table 1 lists instruments used to assess function and other domains. The ADL-PI will serve as our primary outcome measure. It is a 15-item questionnaire that was developed to target the earliest changes in complex daily activities [8]. A performance-based instrument, the Everyday Problems Test [35], will serve as our secondary CdF outcome measure. It is a 42-item paper-pencil test that examines abilities to understand and execute complex daily activities (eg, write a check).

**Table 1 table1:** Measurements conducted under this proposal.

Domain and measures				Time
**Independent variables**				
	Aim 1: neural signature of CdF^a^ (mobile electroencephalographic)		2.5 h including rest	
	Aim 2: MRI^b^ white matter hyperintensity and plasma-based Aβ42^c^/Aβ40/τ		1 h	
	Aim 3: Physical Activity Scale for the Elderly [36] and accelerometry		5 min and 7-d period	
**Outcomes (yearly assessed)**				
	Aim 1: Activities of Daily Living–Prevention Instrument [8]—primary		5 min	
	Aim 1: Everyday Problem Test—secondary		45 min	
	Aims 2 and 3: Incident neural signature of CdF		2.5 h including rest	
**Covariates**				
	Cognition (moderator)	Montreal Cognitive Assessment [37] (moderator aim 1) Wechsler Adults Intelligence Scale IV [38]	55 min	
	Physical function	Quantitative Gait Assessment (ProtoKinetics Movement Analysis Software) [39-41], hand grip strength [42]	15 min	
	Psychosocial	Geriatric Depression Scale [43]; Beck Anxiety Inventory [44]	15 min	
	Dementia risk factors	*ApoE*, obesity, diet [45], social isolation [46], cognitive engagement [47], depression	30 min	
	Medical	Medical history, comorbidities, or medication [30,48]	20 min	
	Sensory	Visual sensory screen [49], Shoebox auditory testing, Vibratron [50], Michigan Neuropathy Screening Instrument [51,52]	15 min	

^a^CdF: complex daily function.

^b^MRI: magnetic resonance imaging.

^c^Aβ: amyloid-β.

Neuroimaging and plasma-based blood testing will be conducted during baseline visits for each participant. C2N Diagnostic will quantify plasma τ217 (nonphosphorylated and phosphorylated) and plasma amyloid (Aβ42, Aβ40), and provide plasma *ApoE* prototyping using liquid chromatography-tandem mass spectrometry platforms (PrecivityAD) [53-55]. Blood samples will be collected and stored in the biorepository at AECOM. Physical activity will be assessed at baseline and during annual in-person visits using the Physical Activity Scale for the Elderly [36] as well as objectively using accelerometry [56] over 7 days (AX3; Axivity Ltd). The Physical Activity Scale for the Elderly [57,58] and AX3 [59] are reliable and valid measures of physical activity.

### Cognitive Diagnoses

Established clinical consensus case conference procedures [60], where participants’ demographic, neuropsychological, neurological, psychosocial, and functional test results are reviewed by a multidisciplinary clinical team consisting of neurologists and neuropsychologists, will be used to determine normal cognitive status. Cognitively unimpaired individuals testing positive for Aβ are classified as preclinical AD [2]. Cognitive status—normal, MCI, and dementia—will be assigned at baseline and during yearly follow-up visits. Individuals with MCI and dementia at baseline are excluded from this project.

### Outcomes

For aim 1, the primary outcome is complex daily functional limitations measured with the ADL–PI, as reported in our previous publication [8]. For aims 2 and 3, the outcome is the incidence of the neural signature of CdF (see section below for definition). All outcome measures are assessed annually over a maximal period of 4 years.

### Ethical Considerations

Protocols for the proposed research project are approved by the AECOM’s IRB (2023-14773). Before enrollment, written consent is obtained from all interested persons who meet the inclusion criteria at the time of the visit. Confidentiality will be preserved by the use of unique ID codes for identification. ID and name associations will be password-protected in an encrypted master file to which only the PI and study coordinator have access. Participant data, including computer data disks, will be kept in a locked room. Participants will receive monetary compensation (US $20 per hour), free lunch, and transportation for participating in this study.

### grEEG Protocol

We designed simple (walking-only) and complex (dual-task walking) gait tasks to measure differential activation (complex minus simple gait). We provide preliminary findings showing that individuals reporting CdF limitations can be characterized by a unique grEEG pattern: weaker sensorimotor activation, measured by pre or postcentral gyrus 13-28 Hz desynchronization, and stronger motor control activation, measured by fronto-medial 3-7 Hz synchronization. Figure 3 shows an individual performing the visual-perturbed walking task. The participant walking on a treadmill wearing an electroencephalographic cap is immersed into a large-scale visual flow field designed to destabilize posture [61]. We superimpose sideway shifts onto a display of dots radiating outward from a central point of extension to create visual perturbations. We validated the task in prior studies [12,15]. Participants wore harnesses for safety.

**Figure 3 figure3:**
[figure not shown]
Participant during the visually perturbed walking task.

### Neural Signatures—Starting With Cognition and Switching to CdF

In our first attempt to identify the neural signature of CdF, we stratified individuals by their cognitive performance [19]. Cognitively normal individuals (Montreal Cognitive Assessment [MoCA] ≥ 22 [62,63]) were dichotomized into low (score of 22-26; n=10) and high (score 27+; n=16) performing groups. We discovered a unique grEEG activation pattern time-locked to the gait cycle in low-cognitive performers: weaker central gyrus β (13-28 Hz) desynchronization paired with stronger fronto-medial θ (3-7 Hz) synchronization during visually perturbed compared to unperturbed walking. We also found correlations between θ synchronization and worse MoCA scores and between β desynchronization and better MoCA scores. Amplitude suppression (ie, desynchronization) of brain oscillatory activity within 8 to 28 Hz over pre as well as postcentral gyrus during movement is considered a neurophysiological marker of sensorimotor activation related to preparation and execution of movement [64-70]. We suggest that posterior parietal and sensorimotor activation during gait adjustment is related to prioritizing inputs from visual, somatosensory, and vestibular systems based on reliability to build accurate proprioception subserving motor output [19]. On the other hand, increased θ activity (ie, synchronization) over the fronto-medial cortex is thought of as a mechanism by which the need for cognitive or motor control is realized and signaled across brain regions [71,72]. In the context of movement, we and others observed fronto-medial θ in moments of postural instability [12,15,73-78].

### Neural Signature of CdF

To test whether this unique grEEG activation pattern also associates with the limitation in CdF, we dichotomized our sample in the following way: (1) compute the difference in activation between unperturbed and perturbed walking; (2) use inverse source localization techniques to estimate intracranial sources of scalp-recorded activity; (3) separate individuals with source localized to fronto-medial regions into groups of weak and strong θ synchronizers using the median; (4) separate individuals without sources in fronto-medial and with sources in sensorimotor region into groups of weak and strong β desynchronizers using the median (we chose right sensorimotor β because effects where strongest for that region and frequency: *P*=.04) [19].

Figure 4 shows preliminary findings in support of our hypothesis: Individuals characterized by a unique grEEG pattern report limitations in CdF to a higher degree.

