## Discussion

### Principal Findings

A major effort aimed at curbing the rapid rise of dementia revolves around early intervention. To substantiate early intervention, it is crucial to enhance the accuracy of early detection. We focus on the neural signature of early limitations in CdF to improve detection. Walking is central to many instrumental and complex activities [9,10]. To determine the neural signature of CdF, our team [11-19] and others [73,87,98-104] have established the validity and reliability of neurophysiological recordings while participants are in motion. We designed novel grEEG protocols for this proposal and selected walking as an activity that, compared to other daily activities (eg, preparing a meal), allows for the use of standardized, reproducible, reliable, and well-tolerated study protocols across participants [30,39,105,106].

Our preliminary findings in 28 older adults without MCI/dementia show that reporting of CdF limitations is associated with a unique grEEG activation pattern: 13-28 Hz central gyrus desynchronization paired with 3-7 Hz fronto-medial synchronization. We term this electroencephalographic activation pattern the neural signature of CdF. This subsample also had higher Aβ burden, smaller brain volume, and WMH in regions affected early by dementia and engaged in less physical exercise.

Some limitations are important to note. The ceiling effect with a majority reporting no limitations in CdF is a concern (eg, in Marshall et al [79] study only 16% reported limitations). However, in our study, 30% of individuals reported limitations [1]. To optimize detection, we choose 2 validated and reliable instruments (self-report [107] and paper-pencil test [35] with numerous dependent variables such as self-assessment, time-to-complete, and number and type of errors to quantify performance) covering a broad range of complex daily activities. Further, different processes denoted by Aβ deposition and WMH and their respective roles in the etiology of AD and other dementias are matters of ongoing debates. The prevalence of amyloid deposition in normal aging warrants consideration of Aβ in concert with phosphorylated τ and neurofilament light assays to recognize the multitude and temporal order of pathological processes leading up to clinical signs.

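### The only operational rule shown for the neural signature, the outcome of Aims 2 and 3, is a preliminary median split on one of two EEG measures; used for incidence, it could count many false onsets

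*Protocol article*

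**What the plan says.** All references are to the protocol article.

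- **Outcome.** Under Outcomes: "For aims 2 and 3, the outcome is the incidence of the neural signature of CdF (see section below for definition". Assessment is annual, for at most 4 years.
- **Operational rule.** Under Neural Signature of CdF, the rule opens with "we dichotomized our sample in the following way". It takes the difference between unperturbed and perturbed walking, localises sources, and then has two branches. The first is "separate individuals with source localized to fronto-medial regions into groups of weak and strong θ synchronizers using the median". The second is "separate individuals without sources in fronto-medial and with sources in sensorimotor region into groups of weak and strong β desynchronizers using the median". The β region was picked from the preliminary data: "we chose right sensorimotor β because effects where strongest for that region and frequency".
- **Pattern in words.** The section on starting with cognition describes "weaker central gyrus β (13-28 Hz) desynchronization paired with stronger fronto-medial θ (3-7 Hz) synchronization". Principal Findings gives "13-28 Hz central gyrus desynchronization paired with 3-7 Hz fronto-medial synchronization" and attaches the name neural signature of CdF to it. The grEEG Protocol section also names both components, with no cut-off.
- **Prevalence.** Prevalence of Unique grEEG Activation uses event-related potentials with a threshold at 1.5 SD from the young-adult mean, and finds 4 of 16 older adults abnormal. The Aim 2 overview reports the pattern in 15 of 28 during dual-task walking.
- **Use as an event.** Statistical Plan Aim 2 drops people with the pattern at baseline and dates the event at the follow-up visit where the pattern is shown. No confirming visit is mentioned. The power statements for Aims 2 and 3 assume an event rate of 0.25.

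**The concern.** A median split is a workable way to describe a small pilot sample once. It is a poor basis for an incident event, for three reasons.

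1. **The cut lies where the distribution is densest.** If it is frozen at baseline, many people sit just below it and cross it through measurement error alone. Removing baseline positives adds regression to the mean, and counting the first positive visit gives error a new chance each year. If the median is instead redrawn at each visit, about half of those classified are positive every time, so the signature cannot become more common.
2. **The measure can change within a person.** θ is used if a fronto-medial source is found, otherwise β. Under Integrated Gait-Electroencephalographic Analysis, a source is kept only if its dipole lies in the brain and explains at least 80% of the variance. Someone scored on θ one year and on β the next could become an incident case without any change.
3. **The descriptions do not agree.** One is either/or on θ and β, one is θ and β together, and one is an ERP threshold from young adults.

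This is the sole outcome of two of the three aims. False onsets unrelated to exposure would pull the hazard ratios for amyloid, white matter hyperintensities and inactivity towards 1, and a null result would be hard to interpret.

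**Working it through.** **The plan's own figures.** 4/16 = 25% (ERP rule). 15/28 = 54% (pattern during dual-task walking), close to what a median split yields. The event rate of 0.25 is stated without derivation. The choice of rule sets the risk set: with 180 people and 20% attrition, a 25% baseline exclusion leaves 180 × 0.8 × 0.75 = 108, and a 50% exclusion leaves 180 × 0.8 × 0.5 = 72.

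**Noise only, frozen cut.** Each visit's score is a stable trait (variance r) plus independent error (variance 1 − r), with no true change. Baseline positives are removed, and the event is the first of up to four annual visits above the cut. The reliability r is assumed. For one follow-up and a median cut there is a closed form, P = arccos(r)/π; for r = 0.9 this is 0.144, and the simulation agrees.

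| r (assumed) | Median, 1 visit | Median, 2 visits | Median, 4 visits | 75th percentile, 4 visits | 75th percentile, two consecutive positives |
|---|---|---|---|---|---|
| 0.7 | 25% | 38% | 51% | 31% | 10% |
| 0.8 | 20% | 31% | 42% | 25% | 8% |
| 0.9 | 14% | 22% | 30% | 17% | 6% |
| 0.95 | 10% | 15% | 21% | 12% | 4% |

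With a median cut and four visits, noise alone exceeds the planned 0.25 at r = 0.7 to 0.9, and comes close to it at 0.95.

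**Redrawn median.** Prevalence among those classified is 50% at every visit by construction. If everyone worsens by 0.5 SD (r = 0.9), incidence at one follow-up is 14%, the pure-noise value, against 41% with a fixed cut.

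**Change of measure.** Assume perfect reliability, a 10% to 30% chance per visit that the other measure is scored, and a θ–β correlation of 0 to 0.5. False incidence after four visits is then 12% to 38%. With r = 0.9 and 20% switching it is 41% to 50%. The article gives no switching frequency.

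**Adding true onsets.** Assumed: 26% true incidence over four visits, a 2-SD shift at onset, true hazard ratio 2.0, 35% exposed, frozen median, no switching.

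| r | Events in people with no true onset by year 4 | Also counting events before a true onset | Observed hazard ratio |
|---|---|---|---|
| 0.7 | 60% | 71% | about 1.2 |
| 0.8 | 55% | 65% | about 1.2 to 1.3 |
| 0.9 | 46% | 55% | about 1.3 to 1.4 |
| 0.95 | 38% | 45% | about 1.5 |

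Ranges reflect separate simulation runs.

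**The case against.** The strongest reply is that the median rule reports how a preliminary sample was divided and is not a rule for the cohort. It is in the past tense, leads into preliminary findings, and its first step covers only visually perturbed walking, one of two planned tasks. The pointer under Outcomes names no heading, and the Aim 1 analysis will still assess which measure relates to functional limitation. The prevalence section shows that the team also works with fixed external cut-offs. The full protocol may hold a cohort cut-off.

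Much of this stands. A reader might infer that the cohort outcome is settled as a median split; the article does not establish that. Nor does anything in it say that the median would be redrawn yearly. That branch is shown only because the text does not exclude it.

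The reply does not remove the point. The Outcomes section sends the reader to a definition below, the section bearing the signature's name holds the only operational θ/β rule, and the one other threshold applies to another measure. The either/or rule also contradicts the paired pattern in the article itself. That goes beyond detail left to a fuller document.

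A second objection is that the size rests on assumed reliability. Principal Findings asserts reliability without a figure. Four follow-ups for everyone is also the worst case, since 4 years is a maximum and 20% attrition is allowed: at r = 0.9 and two visits, noise gives 22%, below 0.25. This is correct and limits the conclusion.

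**Conclusion.** The concern holds in conditional form. The article's only operational rule for the Aims 2 and 3 outcome is a preliminary-sample median split on θ, or on β when no fronto-medial source is found. It conflicts with the paired pattern described elsewhere and with the source of the 25% prevalence. Carried into the Aim 2 event definition with a frozen median, it would record about 51%, 42%, 30% and 21% false incidence over four visits at reliability 0.7, 0.8, 0.9 and 0.95. Switching between measures would add to this by an unknown amount.

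A reader might conclude that most counted events will be false. The documents do not support that as a flat statement, because they give neither reliability nor switching frequency. Under the assumed true-onset scenario, the share runs from 38% to 60% if only people with no true onset by year 4 are counted, and from 45% to 71% if events before onset are included. A large share, possibly most, could be false. A true hazard ratio of 2.0 would then appear as roughly 1.2 to 1.5.

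**What to change.** Before follow-up data are analysed:

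1. **One definition.** Reconcile the grEEG Protocol section, the two neural-signature sections, the prevalence section and Principal Findings. State whether both components are required, and for which walking task. Give a numeric cut-off for θ and for β, away from the median and taken from the study's own baseline distribution. Use young controls only if θ and β data from the same tasks exist for them; the article documents only ERP data. Hold the cut-offs unchanged at all visits.
2. **Same measure(s) per person.** Score the same measure(s) at every visit. Treat a visit where the source is not recovered as missing; do not switch to the other measure.
3. **Supporting analyses.** Analyse annual continuous θ and β in a mixed model alongside the time-to-event analysis. Add a sensitivity analysis that requires two consecutive positive visits.

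A cut-off away from the median reduces false onsets but does not remove them. The 75th-percentile figures above are for a single measure and only illustrate the gain; they do not test a rule requiring both measures.

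**Cost.** No new assessments are needed if the cut-off comes from the study's own baseline data. The price is fewer counted events, some missing visits, and onsets first seen at the last visit that cannot be confirmed. The mixed model still uses the data from those last visits.
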